# Effects of synbiotic supplementation on gut microbiome, serum level of TNF-α, and expression of microRNA-126 and microRNA-146a in patients with type 2 diabetes mellitus: study protocol for a double-blind controlled randomized clinical trial

**DOI:** 10.1186/s13063-020-04236-y

**Published:** 2020-04-14

**Keywords:** Type 2 diabetes mellitus, Synbiotic, Gut microbiome, Tumor necrosis factor-α, MicroRNA

## Abstract

**Background:**

The dramatic increase in the prevalence of type 2 diabetes mellitus (T2DM) is a global major challenge to health. Circulating microRNAs have been suggested as promising biomarkers for different disorders such as diabetes. Imbalances in the gut microbiome have been revealed to contribute to the progression of multiple diseases including T2DM. Recently, the consumption of probiotics and synbiotics in the treatment of various diseases has shown a substantial growth. The anti-diabetes and anti-inflammatory effects of synbiotics have been indicated, which may be due to their beneficial effects on the gut microbiome. However, further research is needed to assess the effects of synbiotics on the microbiota and their impacts on expression of microRNAs relating to T2DM. Thus, we will aim to assess the effects of synbiotics on microbiota, serum level of tumor necrosis factor-α (TNF-α), and expression of microRNA-126 and microRNA-146a in patients with T2DM.

**Methods:**

Seventy-two patients with T2DM will be recruited in this double-blind randomized parallel placebo-controlled clinical trial. After block matching based on age and sex, participants will be randomly assigned to receive 1000 mg/day synbiotic (Familact) or placebo for 12 weeks. The microRNA-126 and microRNA-146a expression levels will be measured by real-time polymerase chain reaction and serum TNF-α level will be assessed by enzyme-linked immunosorbent assay kit at the beginning and at the end of the study. Determination of the gut microbiota will be done by quantitative polymerase chain reaction methods at baseline and at the end of the trial. Biochemical assessments (glycemic and lipid profiles) will also be conducted at onset and end of the study.

**Discussion:**

This is the first randomized controlled trial that will determine the effect of synbiotic supplementation on the gut microbiota and its probable impacts on serum levels of TNF-α and expression of related microRNAs in patients with T2DM.

**Trial registration:**

Iranian Registry of Clinical Trials: IRCT20180624040228N2. Registered on 27 March 2019. http://www.irct.ir/trial/38371.

## Background

Type 2 diabetes mellitus (T2DM) is one of the most common chronic diseases and is one of the most important causes of morbidity and mortality in the world [1]. According to the International Diabetes Federation (IDF), 451 million people had T2DM worldwide in 2017, and the number is expected to reach 693 million adults by 2045 [2]. T2DM is characterized by insulin resistance [3] and chronic low-grade inflammation with abnormal production of inflammatory mediators such as tumor necrosis factor-α (TNF-α) and interleukins [4]; this is often unknown until high blood glucose levels are observed [5]. In patients with T2DM, there is an association between hyperglycemia and increased risk of microvascular complications including nephropathy, retinopathy, and neuropathy, which might damage multiple organs such as the kidneys, eyes, and nerves [6, 7]. Thus, identifying new early biomarkers for diabetes is critical to prevent further serious health problems related to T2DM.

Recent studies have shown that a group of small non-encoding RNAs, namely, microRNAs (miRNAs) can be used as novel biomarkers to detect the progression and predict the complications of diabetes in the early stages of the disease [8, 9]. The miRNAs are relatively small (about 20–24 nucleotides) endogenous RNAs that regulate gene expression by suppressing the post-transcriptional stage [10]. They play important roles in various biological processes ranging from cellular differentiation and metabolism to cancer development [11–13]; consequently, dysregulation of miRNAs is linked to many diseases [9], including T2DM [14–17]. Recent studies showed that the level of circulating microRNA-126 (miR-126) is significantly increased in patients with T2DM compared to non-diabetic people [18, 19]. Moreover, reduced concentrations of microRNA-146a (miR-146a) have been linked to a proinflammatory state related to T2DM [20, 21].

T2DM is a multifactorial disease caused by a combination of genetic and environmental factors [22, 23]. Recent studies have suggested altered composition of the intestinal microbial community as a new candidate that may cause T2DM [24, 25]. The gut microbiome refers to the more than 10^14^ bacteria living in the human gastrointestinal tract [26]. An imbalance in the microbiome is called dysbiosis, which is characterized by decreased diversity or alteration of the gut microbiota pattern, such as reduced numbers of butyrate-producing bacteria, increased abundance of opportunistic pathogens, and decreased short-chain fatty acid-producing bacteria. There is evidence showing that dysbiosis in the gut can cause numerous disease conditions including obesity, T2DM, and neurological disorders, as well as cardiovascular, fatty liver, and inflammatory bowel disease [27, 28]. The role of the microbiome in metabolic disorders may be via affecting the host’s energy balance and metabolism, immune system, inflammatory signals, and the maintenance of the normal function of the intestinal epithelial cells [29, 30]. The gut microbiota can also modulate host miRNA expression [31]. Current findings suggest that patients with T2DM have an altered gut microbiome compared with healthy subjects [32, 33]. Karlsson et al. found a reduction in butyrate-producing bacteria, including *Roseburia* and *Faecalibacterium prausnitzii*, in the gut microbiome of people with T2DM compared with healthy individuals [34]. The composition of the gut microbiome is affected by various environmental factors such as diet and drugs [35]. Due to the enormous impacts of the gut microbiota on T2DM and other chronic diseases, a range of microbiome-targeted therapeutic approaches are recently being explored. These include probiotic and prebiotic interventions, which are relatively safe, non-invasive measures in gut microbiome modulation [36–38].

Probiotics are live microorganisms that can confer beneficial effects on the host regarding the sufficiency of consumption via modulating the gut microbiota [39]. Prebiotics are non-digestible but fermentable fibers which can alter the gut microbiota composition by promoting the growth or activity of beneficial bacteria [36]. Short-chain fatty acids (SCFAs), including acetate, propionate, and butyrate, which are fermented from dietary fiber by the gut bacteria, play a critical role in energy metabolism [40]. Butyrate also has a beneficial role in maintaining the host’s intestinal integrity, leading to the prevention of endotoxemia [41]. Synbiotics are combinations of probiotics and prebiotics such that their health benefits are synergistic [42]. Therefore, it is hypothesized that a change in the intestinal microbiota induced by synbiotic supplementation will modulate expression of related miRNAs and result in improved metabolic health. A recent systematic review and meta-analysis of randomized controlled trials reported a significant change in glucose metabolism and improvement in lipid profiles from synbiotic interventions [43]. Yoo and Kim have shown that probiotics and prebiotics can affect metabolic disorders, including T2DM and cardiovascular disease, by improvement of the gut microbiome, leading to regulation of insulin-signaling and a reduction in cholesterol [44]. Nevertheless, the effects of synbiotics on the gut microbiota composition and their impacts on expression of miRNAs related to T2DM have not yet been investigated in human studies. Few clinical trials have assessed the effects of probiotics on the microbiome and miRNA expression in other chronic diseases; the majority of studies were established in animal models. Recently, one study reported that probiotic treatment in colitic mice exerted positive effects on their immune response by modulating the expression of some miRNAs, perhaps through their ability to modify the intestinal microbiota composition [45].

To the best of our knowledge, there are no clinical trials that assessed the effects of synbiotic treatment on changes of gut microflora composition and expression of miRNAs in patients with T2DM.

### Objectives

The present randomized clinical trial (RCT) aims to investigate the effects of synbiotic supplementation on microbiome composition as well as serum levels of TNF-α and expression of miR-126 and miR-146a in patients with T2DM. Secondary objectives of this trial are to compare the changes in glycemic control indices, including fasting blood sugar, glycosylated hemoglobin (HbA1c), fasting insulin, pancreatic beta cell function, insulin resistance and insulin sensitivity, as well as serum levels of lipids, namely triglycerides (TG), total cholesterol (TC), low-density lipoprotein cholesterol (LDL-C), and high-density lipoprotein cholesterol (HDL-C), between the control and intervention groups.

## Materials and methods

### Study design

This study is a randomized, double-blind, placebo-controlled, parallel clinical trial conducted at the Diabetes Clinic Center in Yazd, Iran. Patients with T2DM will be randomly assigned to a treatment or control group (*n* = 36/group) and will receive either a daily synbiotic (1000 mg) or placebo, respectively, for 12 weeks. An overview of the study is presented in Fig. 1. The Standard Protocol Items: Recommendations for Interventional Trials (SPIRIT) checklist was used to detail the study protocol [46] (see Additional file 1). A SPIRIT diagram including the timepoints of the study is shown in Fig. 2. Any methodological changes in the study design which could affect study procedures or participants’ safety will be discussed by the ethics committee before the study is conducted.

**Fig. 1 Fig1:**
[figure not shown]
Overview of the study

**Fig. 2 Fig2:**
[figure not shown]
SPIRIT figure: template of the content for the schedule of enrollment, interventions, and assessments

### Inclusion criteria

Participants will be eligible for this study if they meet the following criteria:
Men and women who have been diagnosed with T2DM within the previous 6 months and are treated by medication for diabetesAge 25–65 yearsBody mass index 25–35 kg/m^2^6.5% ≤ HbA1c ≤ 8.5%.

### Exclusion criteria

The following people will be excluded from the study: those using alternative therapies with hormones (insulin, corticosteroids) or vitamin supplements; those with chronic kidney, liver, or pulmonary diseases, chronic or acute inflammatory diseases (especially acute pancreatic inflammation and endocarditis), valvular heart disease, or irritable bowel syndrome; those having diabetes complications (nephropathy, cardiomyopathy, retinopathy, diabetic foot ulcers); those with low immune systems (or autoimmune disorders); pregnant or lactating females; those using tobacco or alcohol; those who have consumed probiotics or been treated with antibiotics within the past month; and those following an unusual diet up to 1 month before the study.

### Setting

The subjects’ recruitment process will be advertised through flyers distributed at Diabetes Clinic Centers in Yazd, Iran, affiliated with Shahid Sadoughi University of Medical Sciences, which is the main center in the province in the field of treatment, prevention, research, and services for patients with diabetes. Interested candidates will be invited for the screening process. Blood samples will be obtained from the volunteers, and HbA1c will be measured. Then eligible participants will be invited for their first visit, at which two trained study staff will explain to them the project protocol and procedures in detail and also provide them with an information sheet for their record. Informed consent will be obtained from those who agreed to participate in the study. Demographic information questionnaires including general data such as diseases, medications, and supplements will be administered via interviews. All questionnaires will be approved by the ethics committee of Shahid Sadoughi University of Medical Sciences. Thereafter, participants will be randomly assigned to the intervention or placebo group (*n* = 36/group). Verbal and written instructions on how to take the synbiotic or placebo capsules will be provided at the first visit and at each following visit. All participants, researchers, statistical analysts, and laboratory staff will be blind to the intervention.

### Randomization and blinding

The present study is a two-arm, double-blind parallel RCT in which participants will be randomized 1:1 using the method of stratified block randomization based on age (25–45 and 45–65 years) and sex (male and female), so that the number of samples assigned to each of the groups will be equal [47, 48]. To randomly allocate eligible individuals to the intervention and control groups, computer-generated random numbers will be used, enclosed in sealed envelopes by a third person who will not be involved in the study. Capsules containing the synbiotic and placebo are similar in shape and appearance and will be packed in the same boxes (in terms of color and shape). The capsule boxes will be labeled with codes “A” and “B” by a third party who has no direct involvement in the study. Both participants and investigators will be blinded to the content of the boxes, allocation, and study treatment until data analysis.

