### Intervention

The intervention group will take two capsules of synbiotic per day (one capsule after lunch and one after dinner), and the control group will take two capsules of placebo (containing 500 mg lactose, magnesium stearate, and talc) per day at the same times for 12 weeks. The synbiotic and placebo capsules look and smell identical and will only be differentiated by a label “A” or “B” on the box. The boxes will be labeled by a third party who is not involved directly in this study. Each synbiotic capsule (Familact, produced by Zisttakhmir Company, Tehran, Iran) contains 500-mg levels (109 colony-forming units [CFUs]) of seven beneficial bacteria (*Lactobacillus casei* 3 × 10^8^ CFU/g, *Lactobacillus acidophilus* 2 × 10^8^ CFU/g, *Lactobacillus bulgaricus* 2 × 10^9^ CFU/g, *Lactobacillus rhamnosus* 3 × 10^8^ CFU/g, *Bifidobacterium breve* 2 × 10^8^ CFU/g, *Bifidobacterium longum* 1 × 10^9^ CFU/g, and *Streptococcus thermophilus* 3 × 10^8^ CFU/g), along with a prebiotic fructooligosaccharide (contributing to the growth and activity of probiotics) and other components (lactose, magnesium acetate, talc). Each box contains 30 capsules. Participants will be given six boxes for the entire 3-month intervention (two boxes at the beginning of each month). Moreover, patients will continue to take diabetic medication during the study. The Diabetes Clinic Center in Yazd and Shahid Sadoughi University of Medical Sciences will be responsible to follow up any reports from participants for any potential relevant issues and adverse events. Any possible adverse events will be reported to the medical ethics committee throughout the study. Participants will be informed at the beginning of the study via the consent form that they have the right to withdraw from the study at any time for any reason or even for no reason.

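### Boxes carry only one letter per arm, so staff who handle them can group patients by arm, and one code break unblinds all 72

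*Protocol article*

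**What the plan says.** All of this is in the protocol article.

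- **Labelling.** Randomization and blinding: "The capsule boxes will be labeled with codes “A” and “B” by a third party", described as not directly involved in the trial. The Intervention section adds that the two products look and smell alike and "will only be differentiated by a label “A” or “B” on the box". No participant or kit number on the boxes is described.
- **Blinding claimed.** Randomization and blinding: "Both participants and investigators will be blinded to the content of the boxes, allocation, and study treatment until data analysis". The Setting section extends blinding to analysts and laboratory staff.
- **Allocation.** Patients are allocated 1:1 by "stratified block randomization based on age (25–45 and 45–65 years) and sex", with the computer-generated numbers "enclosed in sealed envelopes by a third person who will not be involved in the study". No block size is given.
- **Contact with the boxes.** Under Intervention, each participant receives six boxes, two at the start of each month. Under Adherence, leftover capsules come back in their boxes at the next visit. Under Study design, the trial runs at one diabetes clinic centre.

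**The concern.** Where each of two letters stands for one of two arms, the letter is the allocation under another name. Anyone who handles boxes for several patients learns who is grouped with whom; only the meaning of the letter stays hidden. The blind for the whole trial then rests on one piece of information. Once that leaks for a single patient, it has leaked for every patient whose letter is known.

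The Discussion counts the double blind among the trial's strengths. The primary outcomes are laboratory assays, so direct assessor bias is limited. Other parts of the trial do depend on how participants and staff behave: the diet and activity records, the adherence calls, the tape-measured waist and hip circumferences, and retention. The centre that can see the letters also follows up adverse events, so reports can be set against letters and a pattern guessed.

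**Working it through.** **Step 1. Inputs.** Two codes and two arms (Randomization and blinding; Intervention). 36 patients per group (Study design; Sample size), so 36 + 36 = 72, which agrees with the Abstract. Six boxes per patient (Intervention). 1:1 stratified blocks, with 2 age bands × 2 sexes = 4 strata. Eligible age 25 to 65 (Inclusion criteria). The block size is not stated and is treated below as an assumption.

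**Step 2. Reach of one code break.** Decoding one letter identifies the 36 patients who carry it. The other letter follows by exclusion, which identifies the other 36. The total is 72 of 72. With a unique number per participant, decoding one box identifies 1 of 72. The letter is also on view often: 72 × 6 = 432 boxes, 216 per letter.

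**Step 3. Set against the blinding claim.** The article says investigators do not know the allocation before data analysis. It also says the letter is what separates the two products. For staff who handle boxes, group membership is visible from the first dispensing. What stays masked is which group is active. The two statements agree only if allocation is read to mean the identity of the treatment and nothing else.

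**Step 4. Predictability of the next letter.** This step assumes a fixed block size of 2m known to the enrolling staff, earlier letters in the stratum visible to them, and complete blocks. An assignment is forced once all m places of one letter are used. The expected number forced per block is 2m/(m + 1), so the share is 1/(m + 1). Check for m = 2: the six possible orders have 2, 1, 1, 1, 1 and 2 forced places, which is 8 of 24, or one third.

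| Assumed block size | Share forced | Of 72 | Correct guesses (chance 50%) |
|---|---|---|---|
| 2 | 1/2 = 50% | 36 | 75% |
| 4 | 1/3 = 33% | 24 | 71% |
| 6 | 1/4 = 25% | 18 | 68% |

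The last column comes from listing every possible block and always guessing the letter with more places left. If block sizes vary or are unknown to staff, the forced share cannot be derived. In every row, what is predicted is a letter, not a treatment.

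**Step 5. Age bands (separate).** Both bands contain 45, which is an eligible age. Ages 25 to 65 inclusive give 41 single years. If ages were spread evenly (an assumption the article does not support), 72/41 ≈ 1.8, so about 2 patients would have no defined stratum.

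**The case against.** The strongest reply is that four larger claims might be inferred from these facts, and the article supports none of them.

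- **That everyone can see who shares an arm.** Participants see only their own boxes unless they compare. Laboratory information is filed by ID number, and laboratory staff and analysts are stated to be blind. The visibility is limited to people who handle boxes for several patients.
- **That upcoming allocations can be predicted.** This needs enrolling staff to see earlier letters stratum by stratum and to know a fixed block size. The article says neither, and an article may leave block size to the full protocol. It does not say that those who enrol also dispense. Sealed envelopes prepared by an uninvolved person still hide the next assignment directly, although they do not stop inference from letters already issued. Steering a patient toward the active arm would also require the code to be broken.
- **That the overlap at 45 contributes to unblinding.** It does not. It leaves one age without a defined stratum and has no bearing on the labels.
- **That the primary results would be biased.** TNF-α, the microRNAs and the stool measures are assayed by staff stated to be blind, so the route to bias is indirect.

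These limits stand. They do not reach the central point. The one-letter-per-arm label is something the article fixes, not something it leaves out, and its statement that only the letter differentiates the products leaves little room for a kit number elsewhere. The consequence for a single code break follows from that alone.

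**Conclusion.** The point holds as a weakness of the labelling scheme. Staff who handle boxes can group patients by arm, and one code break exposes 72 of 72 patients where individual numbers would expose 1 of 72. This sits badly with the claim of blinding to allocation until data analysis. It rests on two assumptions: that the boxes carry no further patient-level code, as the article's wording indicates, and that whoever learns the code also knows the other patients' letters, as staff handling boxes would.

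The forced shares of 50%, 33% and 25% are a conditional worst case, not a finding about this trial. The overlap at age 45 is a real but minor error of stratum definition and should be listed separately. The change should be made, because the failure would be trial-wide, the remedy is cheap, and the Trial status section reports recruitment as ongoing.

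**What to change.** For all remaining enrolments:

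1. The third party who already labels the boxes puts a unique participant or kit number on each participant's boxes, with no pattern by arm, and prints no A or B.
2. The sealed envelopes show that number and no letter.
3. The third party holds the number-to-arm list, so a code break for one patient reveals that patient only.
4. Masked groupings go only to the analyst, at database lock.

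This removes the shared-code failure. It also removes prediction from visible letters whatever the block size, because issued numbers no longer show who is grouped with whom.

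As a separate one-line correction, make the age bands mutually exclusive for remaining enrolments, for example 25–44 and 45–65.

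**Cost.** A small relabelling effort by the third party and upkeep of one list, with no extra patients, visits or analyses. The gain is partial. Patients already holding lettered boxes stay under the two-letter code, and the article does not say how many enrolments remain.

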### Sample size

The required sample size is calculated based on data from a previous human study, which assessed the effects of probiotic yogurt consumption on inflammatory biomarkers [49] by considering the serum level of TNF-α as the primary variable. A mean difference in serum TNF-α levels of 0.84 pg/mL between the two groups is aimed to be detected for a specified α of 0.05 and a study power of 80%. Based on the proposed formula for parallel clinical trials [50], we reached a sample size of 33 participants in each group. Assuming a possible drop-out rate of 10%, 36 patients will be enrolled in each group. G*Power 3.1 software was used for the sample size calculation.

